### Randomisation and masking

Randomisation will be completed using simple randomisation with a 1:1:1 allocation ratio. A pre-randomised list with random sorting of the three trial arms will be generated in Microsoft Excel using the = RAND() function. As each participant enrols in the study, he/she will be sequentially assigned to the corresponding group in the pre-randomised list. The entire randomisation procedure will be completed by a trained research assistant who is not involved in other aspects of the trial. The project therapists and clinical assessors will be blinded to the group allocation. We do not anticipate any requirement for unblinding but if required, the Trial Manager, Data Coordinator, and Implementation Support Facilitators will have access to group allocations and any unblinding will be reported.

### Procedures

Interested individuals can register for the study using an online application form and will be initially screened based on age, ISI score ≥ 9, and rMEQ score ≤ 11. Potential eligible individuals will then be invited to attend a face-to-face clinical interview to ascertain their eligibility for the trial. The diagnoses of sleep disorders and psychiatric disorders will be ascertained using the Diagnostic Interview for Sleep Patterns and Disorders [42] and the Mini International Neuropsychological Interview, respectively [43]. After confirming their eligibility, participants will be randomised to one of the following groups: CBTI + BLT, CBTI-BLT, and WL. Assessments are scheduled at pre-treatment (Week 0), during treatment (Week 2 and Week 4), and post-treatment (Week 7). Assessments at Week 2 and Week 4 will consist of two self-report measures (Insomnia Severity Index and Hospital Anxiety and Depression Scale) for monitoring the clinical status of the participants. Actigraphy will also be used in Week 4 to objectively monitor sleep and circadian-related changes and light exposure across the groups. The two active intervention arms (CBTI + BLT and CBTI-BLT) will be additionally followed up at 1 month and 6 months after the conclusion of the last group session. Participants in the WL group will be offered the treatment (either CBTI + BLT or CBTI-BLT) after completing the post-wait assessment. Figure 1 shows the study flowchart, and the study schedule is summarised in Table 1. Participants will receive HKD 500 (~ USD 64) at the end of the follow-up period as a token of appreciation of their participation in this trial.

**Fig. 1 Fig1:**
[figure not shown]
Flowchart of study design. CBTI + BLT cognitive behavioural therapy with active bright light therapy, CBTI-BLT cognitive behavioural therapy with placebo light therapy, HADS Hospital Anxiety and Depression Scale, ISI Insomnia Severity Index, rMEQ reduced Morningness-Eveningness Scale, WL waitlist control

**Table 1 Tab1:** Study schedule

Timeline	Baseline			Intervention	Post-treatment		
	Enrolment	Pre-treatment assessment	Allocation	Treatment	Post-treatment assessment	1-month follow-up	6-month follow-up
Enrolment							
Screening for eligibility	●						
Informed consent	●						
Allocation			●				
Intervention							
CBTI + BLT		●		●	●	●	●
CBTI-BLT		●		●	●	●	●
Waitlist Control		●			●		
Data Collection							
Primary outcomes		●			●	●	●
ISI		●		●	●	●	●
Secondary outcomes		●			●	●	●
PSQI		●			●	●	●
MCTQ		●			●	●	●
CDRS		●			●	●	●
HADS		●		●	●	●	●
DSI-SS		●			●	●	●
PDSS		●			●	●	●
MFI		●			●	●	●
KIDSCREEN-27		●			●	●	●
Sleep diary parameters		●		●	●	●	●
Actigraphy parameters		●			●	●	●
PSG parameters		●			●		
DLMO assessment		●			●		
Neurocognitive assessments		●			●		●

*CSRS* the Children’s depression rating scale, *DLMO* Dim-light melatonin onset, *DSI-SS* Depressive symptoms inventory suicidality subscale, *HADS* Hospital anxiety and depression scale, *ISI* Insomnia severity index, *MCTQ* Munch chronotype questionnaire, *MFI* Multidimensional fatigue inventory, *PDSS* Paediatric daytime sleepiness scale, *PSQI* Pittsburgh sleep quality index

### Measures

#### Primary outcomes

The primary outcome is the change in insomnia symptoms as measured by the Insomnia Severity Index (ISI). The ISI is a seven-item self-rated scale designed to measure one’s insomnia problems, satisfaction with sleep, noticeability and worries towards one’s sleep problems, and insomnia-related interference with daily life. The possible score ranges from 0 to 28, where a higher score indicates greater insomnia severity. The ISI has been validated in local youths demonstrating good construct validity and high internal consistency with a Cronbach’s alpha of 0.83 [40].

#### Secondary outcomes

The secondary outcomes include changes in subjective sleep quality as measured by the Pittsburgh Sleep Quality Index (PSQI) [44], self-report chronotype as measured by the Munch Chronotype Questionnaire (MCTQ) [45], clinician-rated depressive symptoms as measured by the Children’s Depression Rating Scale (CDRS) [46], self-report mood symptoms as measured by the Hospital Anxiety and Depression Scale (HADS) [47], and suicidal ideation as measured by the Depressive Symptoms Inventory Suicidality Subscale (DSI-SS) [48]. Daytime functioning is subjectively assessed by the Paediatric Daytime Sleepiness Scale (PDSS) for daytime sleepiness and the Multidimensional Fatigue Inventory (MFI) for daytime fatigue [49, 50]. Secondary outcomes also include a change in the quality of life as measured by the KIDSCREEN-27 and the overall severity of clinical symptoms assessed by clinicians using the Clinical Global Impression Scale [51].

Other sleep-related outcomes will be evaluated subjectively using a sleep diary and objectively using actigraphy. Participants will be asked to complete a 7-day sleep diary while wearing a wrist actigraphy (Actiwatch Spectrum Plus, Philips Respironics). The outcomes to be analysed from the sleep diary and actigraphy are sleep onset time, wake time, total time in bed (TIB), total sleep time (TST), sleep onset latency (SOL), wake after sleep onset (WASO), and sleep efficiency (SE) across the recording period. Epoch-by-epoch actigraphy data will be extracted using cosinor and nonparametric analysis for circadian rhythm computation [52, 53]. Circadian parameters derived from cosinor analysis include the acrophase, amplitude, and MESOR, while circadian parameters derived from the nonparametric analysis include interdaily stability, intradaily variability, relative amplitude, M10 onset (10 h of maximal activity), and L5 onset (5 h of the least activity). Table 2 summarises the circadian parameters from the actigraphy computation.

**Table 2 Tab2:** Circadian parameters derived from actigraphy circadian computations

Variables	Explanations
Cosinor analysis	
Acrophase	Time of maximum activity (peak). Express as clock time
Amplitude	Differences in distance from the peak to the nadir
MESOR	The mean activity level of the fitted curve
Non-parametric analysis	
L5/M10 onset	Time of onset of the five least active hours (presumed to represent sleep) and the ten most active hours (presumed to represent daytime activity). Express as clock time
Intradaily variability (IV)	An index ranging from 0–1 quantifies the degree of rhythm fragmentation. A higher value reflects greater fragmentation, reflecting more daytime napping or nocturnal awakening
Interdaily stability (IS)	An index ranging from 0–1 reflects the synchronisation of rhythm to the light–dark cycle. A higher value reflects better synchronisation
Relative amplitude (RA)	Normalised differences in distance from L5 to M10. A higher value reflects the greater robustness of the circadian rhythm

Participants will also be invited to complete a series of computerised neurocognitive tasks to assess objective cognitive performance. The list of computerised neurocognitive tasks is summarised in Table 3.

**Table 3 Tab3:** List of neurocognitive tasks

Tasks	Cognitive domains
Balloon Analogue Risk Task	Risk-taking and decision making
Chinese Auditory Verbal Learning Task	Episodic memory
Digit Span (forward and backwards)	Working memory
N-back Task	Working memory
Go/No-Go Task	Inhibitory control
Trail Making Test	Visual attention and task switching/executive function
Wisconsin Card Sorting Test	Set shifting/executive function
Dot-probe Task	Attention bias

#### Other secondary measures

Due to limited funding resources, only half of the participants in the two treatment arms will be invited to complete a two-night in-laboratory assessment at baseline and post-treatment to objectively assess one’s sleep and circadian phase. Data collection will start after more than 50% of participants have been enrolled. The first night will serve as the adaptation night, and dim-light melatonin onset (DLMO) assessment will be conducted according to the previously published protocol [54]. In brief, participants will be asked to provide a total of 17 salivary samples in 30-min intervals starting 6 h before and continuing for 2 h after the habitual bedtime under a dim light condition with the ambient light level maintained below 10 lx. The salivary melatonin specimens will then be assayed using ultra-performance liquid chromatography-tandem mass spectrometry. The clock time of DLMO, calculated with linear interpolation when the melatonin concentration exceeded and remained above an absolute threshold of 12.9 pmol/L for at least two additional samples, will be used to reflect the circadian phase [55]. On the second laboratory night, participants will complete a level I polysomnography (PSG; Grael PSG Amplifiers and Recorders, Compumedics). Electrodes and sensors will be placed according to the American Academy of Sleep Medicine Manual for Scoring of Sleep and Associated Events [56]. PSG signals will be acquired and analysed using Compumedics Profusion SLEEP4 and stored securely at the Sleep Research Clinic and Laboratory at the University of Hong Kong. PSG recordings will then be scored by registered polysomnographic technologists who are blinded from the group allocations. Polysomnography-based sleep parameters that are considered as the secondary outcomes include total time in bed (PSG-TIB), total sleep time (PSG-TST), sleep onset latency (PSG-SOL), wake after sleep onset (PSG-WASO), and sleep efficiency (PSG-SE).

### Intervention

#### Cognitive behavioural therapy for insomnia

The CBT-I programme consists of six weekly sessions, 90 min each. The sessions will be conducted in a group format (four to six participants per group) and facilitated by trained therapists. The group sessions are structured and adopted from a well-established protocol for treating insomnia with additional emphasis on the effect of the circadian rhythm [57]. The programme aims to address the behavioural, cognitive, and physiological factors perpetuating insomnia. Table 4 summarises the session content of the CBT-I programme.

**Table 4 Tab4:** Summary of the CBT-I programme

Session	Topics
1	• Programme overview • Psychoeducation on normal sleep, circadian rhythm, and insomnia • Introduction to 3Ps model of insomnia and case formulation • Introduction to the use of a sleep diary
2	• Review of sleep diary • Introduction to bright light therapy using Re-Timer • Behavioural strategies (sleep restrictions, stimulus control) • Sleep hygiene education • Setting sleep windows
3	• Review of sleep diary and use of Re-Timer and adjustment of sleep windows • Introduction to different treatment approaches for insomnia • Stress management and relaxation exercises • Constructive worry techniques
4	• Review of sleep diary and use of Re-Timer and adjustment of sleep windows • Cognitive restructuring Part I
5	• Review of sleep diary and use of Re-Timer and adjustment of sleep windows • Cognitive restructuring Part II
6	• Review of sleep diary and use of Re-Timer and adjustment of sleep windows • Review of the programme • Consolidating gains and relapse prevention

#### Bright light therapy

Participants in both intervention arms will be instructed to wear a portable light therapy device for 30 min daily immediately after awakening (Re-Timer; https://www.re-timer.com). Re-Timer is equipped with four light-emitting diodes (LEDs; two on each side) emitting a constant green light (per manufacturer’s manual, 500 nm dominant wavelength at 506 lx). The efficacy and safety of the Re-Timer have been reported by previous research [31, 58, 59]. The CBTI + BLT group receiving an active BLT treatment will be provided with the original Re-Timer, whereas the CBTI-BLT group receiving the placebo BLT treatment will be provided with a modified Re-Timer. The modified Re-Timer has red cellophane filters and red colour cardboard paper (250 g/m^2^) covering the LEDs, which turns the visual light spectrum towards red colour and blocks most of the light emitted from the LEDs (< 10 lx). This level of the light emitted from the modified Re-Timer is considered insufficient to have a phase-shifting effect on the circadian rhythm [60]. During each group session, the therapist will individually review and prescribe timing for light therapy for each participant based on their sleep diary completed in the previous week, aiming to advance one’s rise time and gradually optimise the sleep schedule. The daily sleep diary will be used to record participants’ usage of the Re-Timer to analyse adherence to BLT intervention.

#### Treatment integrity and quality assurance

All intervention sessions will be delivered by clinical psychologists or doctoral students who have received extensive training in behavioural sleep medicine and circadian science. All therapists will meet regularly during the study to discuss specific issues regarding the implementation of the trial protocol and to ensure the consistency of the implementation of the treatment protocol. All therapy sessions will be video recorded, and a subset of the recordings (20%) will be randomly selected to be reviewed and closely scrutinised by the blind judges based on a list of quality checkpoints.

#### Safety and adverse events

The likelihood of having serious adverse events during this trial is expected to be minimal. Both CBT-I and light therapy are generally well-tolerated. A systematic review of 99 studies on the randomised controlled trials of CBT-I showed no serious adverse events attributed to CBT-I [61]. Similarly, a review of 43 studies on bright light therapy showed no evidence of ocular damage due to light therapy [62]. Nonetheless, there have been reports of an increased risk of hypomania (risk ratio = 4.91, 95% CI 1.66 to 14.46), agitation, headache, blurred vision, and eye irritation in the use of bright light therapy [63]. As such, the HADS and an adverse effects checklist [64] will be used biweekly during treatment (i.e. Week 2 and Week 4) and follow-up assessment to monitor potential mood changes, the frequency of adverse events, and the related daytime impairment severity. In addition, the research clinician will evaluate any suicidal thoughts and behaviour, as well as non-suicidal self-injury, during the intervention period. Participants will be removed from the study and referred for open treatment in the case of serious adverse events (e.g. acute suicide risk or attempt).

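### Two sections disagree on whether the adverse effects checklist is given at Weeks 2 and 4, and neither clearly places it at pre-treatment or Week 7, so roughly 25-60% of light use follows the last clearly named on-treatment check

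*Protocol article*

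**What the plan says.** The section Safety and adverse events lists effects reported with bright light: hypomania (risk ratio 4.91, 95% CI 1.66 to 14.46), agitation, headache, blurred vision and eye irritation. In response it pairs the HADS with a second instrument: "adverse effects checklist [64] will be used biweekly during treatment (i.e. Week 2 and Week 4) and follow-up assessment to monitor potential mood changes". Its stated purpose also includes recording how often adverse events occur and how far they impair daytime life. A research clinician separately evaluates suicidality and self-injury during the intervention.

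Procedures sets the calendar: "Assessments are scheduled at pre-treatment (Week 0), during treatment (Week 2 and Week 4), and post-treatment (Week 7"). It then fixes the content of the two mid-treatment visits: "Assessments at Week 2 and Week 4 will consist of two self-report measures (Insomnia Severity Index and Hospital Anxiety and Depression Scale"). The checklist is not mentioned there. The active arms "will be additionally followed up at 1 month and 6 months after the conclusion of the last group session".

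Table 1 ("Study schedule") has no row for the checklist. It shows the HADS at pre-treatment, during treatment, post-treatment and both follow-ups.

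On exposure, "The CBT-I programme consists of six weekly sessions, 90 min each". Table 4 places "Introduction to bright light therapy using Re-Timer" in session 2 and a review of device use in sessions 3 to 6. The Bright light therapy section says: "Participants in both intervention arms will be instructed to wear a portable light therapy device for 30 min daily immediately after awakening". The Abstract has the device used for the whole intervention period.

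**The concern.** The checklist is the only instrument named for headache, blurred vision and eye irritation. The HADS measures anxiety and depression, the clinician's evaluation covers suicidality and self-injury, and the weekly device review is described in terms of use and timing. What is known about these effects therefore depends on when the checklist is given, and the article leaves that uncertain in three ways.

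- **Weeks 2 and 4.** One section includes the checklist. The other counts two measures and leaves it out.
- **Fit to exposure.** The on-treatment schedule, as spelled out, ends at Week 4, although light starts only in session 2 and continues to the end of the intervention. The first check comes very early in light use, and a sizeable part of light use follows the second.
- **Baseline.** No pre-treatment administration is named, although complaints such as headache or agitation may be present before treatment. Without one, an individual complaint cannot be classed as new or worse.

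At stake is how completely side effects of the light device are captured, and how firm a statement on tolerability the trial can support. The Discussion already speaks of both approaches as potentially safe.

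**Working it through.** The plan gives no figure to reproduce here. The check compares the texts and then counts days of light use.

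**Step 1: the texts side by side**

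| Visit | Safety and adverse events | Procedures | Table 1 |
|---|---|---|---|
| Pre-treatment, Week 0 | checklist not named | checklist not named | no checklist row; HADS shown |
| Weeks 2 and 4 | HADS and checklist | ISI and HADS, counted as two | no checklist row; ISI and HADS shown |
| Post-treatment, Week 7 | not clearly named | checklist not named | no checklist row; HADS shown |
| 1 and 6 months | named as follow-up | checklist not named | no checklist row; HADS shown |

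The sections agree on the HADS at Weeks 2 and 4 and differ on the checklist. Procedures also names the Week 7 visit separately from the two follow-ups. On that usage, follow-up in the safety section means 1 and 6 months.

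**Step 2: inputs for the exposure count**

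- Last clearly named on-treatment check: Week 4, day 28 (Safety and adverse events).
- Start of light, S: session 2 (Table 4). The calendar position of session 1 is not stated. Assumption A: session k falls in Week k, so S = day 14 and session 6 = day 42. Assumption B: session 1 falls at Week 0, so S = day 7 and session 6 = day 35.
- End of light, E: assumed to be session 6 or the Week 7 visit (day 49).

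**Step 3: formulas**

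- Light use before the Week 2 check = 14 − S
- Light use before the Week 4 check = 28 − S
- Share of light use after Week 4 = (E − 28) / (E − S)

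**Step 4: results**

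| Assumption | Before Week 2 check | Before Week 4 check | Share after Week 4, E = session 6 | Share after Week 4, E = Week 7 |
|---|---|---|---|---|
| A (S = 14) | 14 − 14 = 0 days | 28 − 14 = 14 days | (42 − 28)/(42 − 14) = 14/28 = 50% | (49 − 28)/(49 − 14) = 21/35 = 60% |
| B (S = 7) | 14 − 7 = 7 days | 28 − 7 = 21 days | (35 − 28)/(35 − 7) = 7/28 = 25% | (49 − 28)/(49 − 7) = 21/42 = 50% |

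So the Week 2 check sees 0-7 days of light and the Week 4 check follows 14-21 days. Between 25% and 60% of light use comes after the last clearly named on-treatment check, and 40-75% comes before it. The next clearly named check is one month after the last session.

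**The case against.** Much can be said for the plan, and several points stand.

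- **Side effects are not largely unobserved.** A reader might infer that they are. Under the safety section, the Week 4 check follows two to three weeks of light, 40-75% of light use precedes it, and a further check at follow-up is stated. The inference would need Procedures to override the safety section, and nothing in the article says that it does.
- **Week 7 may be covered.** The safety sentence gives the HADS and the checklist one joint timing, and Table 1 shows the HADS at post-treatment. The sentence also omits the pre-treatment HADS that Table 1 shows, so it is evidently not a full list of occasions. The fair statement is that Week 7 is not clearly named. It cannot be called absent.
- **The recall period is not given.** A later administration may reach back over earlier weeks.
- **Table 1 proves little by itself.** It also omits the Clinical Global Impression Scale, TSS, TCAS and CEQ, all named in the text. A journal article may leave a full visit grid to the detailed protocol.
- **No bias between the light arms is shown.** A reader might infer a pull towards no difference in side effects. The two light arms are randomised and concurrent, so prior complaints are balanced in expectation. A very early Week 2 check would dilute the contrast only if pooled with Week 4, and no pooling is stated.

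One defence is weaker. It says that the count of two in Procedures is not exhaustive, because the next sentence adds actigraphy at Week 4. That sentence does show that the visit holds more than questionnaires. But it names the addition, whereas the checklist is named nowhere in Procedures. Condensing an article can explain a missing table row more easily than a counted list that differs from another section.

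**Conclusion.** The point holds as a disagreement between two sections and an incompletely stated schedule. Procedures and the safety section differ on whether the checklist is given at Weeks 2 and 4. No pre-treatment administration is named, and Week 7 is not clearly named. The 25-60% range for light use after Week 4 assumes that light starts at session 2, that session 1 falls in Week 0 or Week 1, and that light ends at session 6 or Week 7. If the follow-up wording was meant to include Week 7, or if the checklist's recall is long, the practical gap is smaller. The article settles neither question. The documents support incomplete and uncertain capture of side effects. They do not support a claim that effects go mostly unseen or that the comparison of bright with placebo light is biased. The point is worth acting on because the remedy uses visits that already take place.

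**What to change.** 1. Reconcile Procedures, the safety section and Table 1 so that all three show the checklist at Weeks 2 and 4.
2. Add the checklist explicitly at the existing pre-treatment and Week 7 visits, and say which visits the word follow-up covers.
3. Set the recall so that each on-treatment and later administration covers the time since the previous visit.
4. Report adverse effects by arm, as new or worse than baseline where a baseline exists.
5. Data collection began on 1 March 2020 and was expected to end in December 2023, while this version is dated 26 September 2023. For participants already past the visits concerned, state which administrations were actually made and limit the safety conclusions accordingly.

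The cost is edits to two sections, one table row and a slight questionnaire burden at existing visits. Missed pre-treatment or Week 7 checks cannot be recovered, so for those participants the gain is in accurate reporting only.

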### Participants

Participants aged 12–24 years will be recruited from the community, local schools, universities, and hospitals via social media promotion, flyers, mass emails, and invitation letters sent to all relevant institutions in Hong Kong. This age range was chosen to reflect the puberty onset and a wider span of adolescence till the early phase of young adulthood, where sleep and circadian issues continue to be prevalent [13]. The inclusion criteria are as follows: (1) having a chief complaint of difficulty initiating sleep at least three times a week for 3 months or more, with clinically significant impairment or distress, (2) scored ≥ 9 on the Insomnia Severity Index (ISI) [39], a suggested cut-off for clinical insomnia in youths [40], (3) scored ≤ 11 on the reduced Morningness-Eveningness Questionnaire (rMEQ) [41], the conventional cut-off for classifying evening type, (4) having a sleep onset time at or later than 23:15 (for those aged 12), 23:30 (for those aged 13–14), or 00:00 (for those aged 15 or above) for at least three nights per week, as confirmed by a prospective 7-day sleep diary. Participants will be excluded if they meet the following exclusion criteria: (1) having a current diagnosis or a history of manic or hypomanic episodes, schizophrenia spectrum disorders, neurodevelopmental disorders, organic mental disorders, intellectual disabilities, or substance abuse or dependence, (2) having a prominent medical condition known to interfere with sleep continuity and quality (e.g. eczema, gastro-oesophageal reflux disease), (3) having a clinically diagnosed sleep disorder that may disrupt sleep continuity and quality (e.g. narcolepsy, sleep-disordered breathing, restless leg syndrome) except for insomnia disorder and delayed sleep–wake phase disorder, (4) concurrent and regular use of medications known to affect sleep continuity and quality (e.g. hypnotics), (5) initiation or change of medications that could interfere with the circadian rhythm (e.g. lithium, melatonin supplements, melatonin agonist) within the past 3 months, (6) presence of clinically significant suicidal ideation with a plan or an attempt, (7) concurrently receiving any forms of structured psychotherapy, (8) presence of hearing or speech deficit or eye disease (e.g. retinal blindness, severe cataract), (9) being a night shift worker, and (10) had trans-meridian flight in the past 3 months or during the study.

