#### Main analysis

The main analyses will be conducted following the intention-to-treat principle. Multilevel modelling (MLM) with restricted maximum likelihood estimation and an unstructured variance–covariance matrix will be used to analyse the main hypotheses on outcome measures. The use of MLM in analysing RCT data has the advantage of accounting for individual differences as a random effect [67–69]. MLM also has advantages over the traditional general linear model approach (e.g. mixed model repeated measures ANOVA) as it is unaffected by randomly missing data and can handle both time-dependent and independent covariates [67, 69]. Missing data for dependent variables will be assumed to be missing at random and accounted for by the maximum likelihood estimation. Two sets of MLMs will be conducted; one will include three treatment arms (CBTI + BLT vs CBTI-BLT vs WL) and two timepoints (pre-treatment vs post-treatment) as fixed effects; the second set will consist of two treatment arms (CBTI + BLT vs CBTI-BLT) and four timepoints (pre-treatment vs post-treatment vs 1-month follow-up vs 6-month follow-up) as fixed effects. The treatment × time interaction will also be included as a fixed effect on both MLMs and will be considered the treatment effect, while repeated measures will be nested within individual participants as random intercepts. A *p*-value of 0.05 represents statistical significance in all analyses. The *p*-values on outcome measures will be adjusted using the Benjamini–Hochberg procedure with a false discovery rate set as 20% to account for multiple comparisons.

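### The serious-adverse-event rule takes the participant out of the study rather than only off treatment, so later mood, suicidality and safety data would be lost for an outcome-related reason (minor)

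*Protocol article*

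**What the plan says.** All of the text is in the protocol article.

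- **Safety and adverse events.** The rule reads "Participants will be removed from the study and referred for open treatment in the case of serious adverse events"; the example given is acute suicide risk or attempt. The same section schedules the HADS and an adverse effects checklist at Weeks 2 and 4 and at "follow-up assessment to monitor potential mood changes, the frequency of adverse events, and the related daytime impairment severity". On frequency it says "The likelihood of having serious adverse events during this trial is expected to be minimal", without giving a rate.
- **Participants.** Entry is barred by "presence of clinically significant suicidal ideation with a plan or an attempt".
- **Secondary outcomes and Table 1.** Suicidal ideation (DSI-SS) and mood (HADS, CDRS) are secondary outcomes, measured before and after treatment and, in the two active arms, at 1 and 6 months. Of these three, only the HADS also has on-treatment values.
- **Procedures.** The active arms "will be additionally followed up at 1 month and 6 months after the conclusion of the last group session"; the waitlist arm has no assessment beyond post-wait as randomised.
- **Main analysis.** The analysis follows intention to treat. "Missing data for dependent variables will be assumed to be missing at random", and the three-arm model uses "two timepoints (pre-treatment vs post-treatment) as fixed effects".

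**The concern.** Stopping a treatment and leaving a study are different events, and the rule merges them. If staff follow it as written, two kinds of information go.

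The first is later DSI-SS, HADS and CDRS scores. The example trigger is close to what these scales measure, so the data are missing because of the participant's state on the outcome. The three-arm model holds only pre- and post-treatment values, so someone removed during treatment contributes a baseline alone. Nothing in the model reflects the deterioration that led to removal. Missing at random is therefore doubtful for these few people.

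The second is the trial's own safety record. The follow-up checklist and HADS exist to track mood change and adverse events, yet the participants with the most serious events would be the ones without them.

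Data collected before removal are kept, so this does not contradict intention to treat.

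**Working it through.** **The text.** The article gives no figure to reproduce on this point, so the first check is of wording. The rule's object is the study. No section says that removed participants keep attending assessments, and none says outright that assessments stop. That assessments end is an inference from the wording, and the plain one.

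**Scale.** No event rate is given, so what follows is an illustration in SD units of a secondary outcome.

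Inputs:
- From Sample size estimation: 48 per arm and 30% attrition, giving 48 × 0.7 = 33.6, taken as 34 per arm.
- Assumed: normal scores; pre-post correlation 0.5; a baseline-adjusted between-arm difference; a latent risk correlated 0.3, 0.5 or 0.8 with the post score.

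*Signed bound.* Shift = (extra removals / n) × (gap between unseen and predicted score).
- One extra removal and a gap of 1 SD: 1/34 = 0.029 SD, or 1/48 = 0.021 SD.
- The gap can take either sign. A range of -1 to +1 SD therefore gives about -0.03 to +0.03 SD (34 per arm) or -0.02 to +0.02 SD (48 per arm), and twice that for two extra removals.

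*Standard error without removal.* With residual variance 1 - 0.5² = 0.75:
- √(2 × 0.75/34) = 0.210 SD (simulated 0.212)
- √(2 × 0.75/48) = 0.177 SD (simulated 0.177)

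*Simulation.* 40,000 runs per cell, the same data analysed with and without removal. Unseen scores are taken to be worse than predicted. Shifts in SD, for risk correlations 0.3 / 0.5 / 0.8:

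| Who is removed | Removals by arm | 34 per arm | 48 per arm |
|---|---|---|---|
| Highest risk | 1 v 0 | 0.014 / 0.024 / 0.039 | 0.011 / 0.018 / 0.029 |
| Highest risk | 2 v 0 | 0.027 / 0.045 / 0.072 | 0.020 / 0.033 / 0.054 |
| Random, top quarter of risk | 1 v 0 | 0.009 / 0.014 / 0.023 | 0.006 / 0.010 / 0.016 |
| Random, top quarter of risk | 2 v 0 | 0.019 / 0.030 / 0.048 | 0.012 / 0.020 / 0.033 |

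With 1 v 1 removals the shift is within 0.0002 SD of zero in every cell.

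*Hand check of the largest 1 v 0 cell.* The expected maximum of 34 standard normals is about 2.1. The covariance of risk with the baseline-adjusted score is 0.8 - 0.5 × 0.4 = 0.6. Then 2.1 × 0.6/33 ≈ 0.038 SD, against 0.039 simulated.

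*Effect on a nominal 5% two-sided test, worst cells.*
- 1 v 0: 0.039/0.212 = 0.18 standard errors; Φ(-1.78) + Φ(-2.14) ≈ 5.4%.
- 2 v 0: 0.072/0.212 = 0.34 standard errors; Φ(-1.62) + Φ(-2.30) ≈ 6.3%.

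**Timing.** Under Trial status, this version is dated 26 September 2023 and data collection was due to end in December 2023. An active-arm participant whose 6-month visit falls by 31 December finished treatment by about 30 June, and had the 1-month visit by about 30 July. From 30 June to 26 September is 31 + 31 + 26 = 88 days. For the active arms, a change made with this version could therefore recover only 6-month data, not post-treatment values for the three-arm model.

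**The case against.** The strongest reply is that the step from removal to lost data rests on silence. A journal article condenses a fuller protocol, where handling after discontinuation commonly sits. The rule couples removal with referral for open treatment, and the preceding sentence places the suicidality review in the intervention period, so it may mean only that trial treatment stops. This reading is possible. But the article does more than leave a gap: it states a rule, and the rule names the study. If the looser meaning was intended, the same one-sentence clarification is needed.

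Second, releasing a young person in crisis from research burden is a defensible clinical choice. That stands, and it is why continued assessment should depend on consent and clinical judgement, with the referral untouched.

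Third, the effect is trivial beside the anticipated 30% attrition (0.3 × 48, about 14 per arm), on which missing at random depends far more. The 6.3% figure also needs several unfavourable assumptions together: two removals against none, the two highest-risk participants, a 0.8 correlation, the smaller arm size, and unseen scores worse than predicted. This is right about the between-arm comparison. It does not answer the loss of safety follow-up in the participants with the gravest events.

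Fourth, the change comes too late to recover much. That is largely true and limits its value.

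**Conclusion.** The concern holds, as a minor one. Followed as written, the rule loses later suicidality, mood and adverse-effect data for an outcome-related reason in the few participants who have a serious event. A comparison between arms is touched only if removals are unequal, which the document does not show. One extra removal then shifts a secondary outcome by 0.006 to 0.039 SD (3% to 18% of a standard error), and two extra by 0.012 to 0.072 SD (7% to 34%). These figures rest on the assumed correlations, 34 or 48 per arm, and unseen scores worse than predicted. The true direction is uncertain, because scores could be worse because of the event or better after open treatment. No bias has been demonstrated. The conclusion also rests on taking removal from the study at its plain meaning.

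**What to change.** Keep the referral and reword the rule. A serious adverse event ends the trial intervention. The participant stays in the intention-to-treat set with all data already collected and, with consent and if clinically appropriate, completes the remaining scheduled questionnaires and adverse effects checklist. Report the number of such removals and their reasons by arm.

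A sensitivity analysis that adds the Week 2 and Week 4 values is optional. It would help only ISI and HADS, since DSI-SS and CDRS have no on-treatment measurement in Table 1.

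The cost is one sentence and a few consented questionnaires. The downside is that later scores would include the effect of open treatment and would not show what would have happened without it. Given the dates, further assessment in the active arms could add only 6-month data. Reporting removals by arm applies to everyone randomised.
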